## Methods/Design

### Design

This is a randomised, double-blind, placebo-controlled clinical trial that tests active and inactive versions of an air purifier. The air purifiers are equipped with monitors to measure the number of hours they operate. AR patients sensitive to the allergens produced by *Artemisia* pollen will be assigned randomly to two groups of equal numbers. All patients will accept a 4-week treatment period and a 4-week observation period. Patient evaluation will be undertaken at baseline (day 0) and on days 7, 14, 21, 28, and 56 (Table 1). Figure 1 displays a flowchart of the study design. Specific tests that will be conducted at each follow-up occasion are outlined in Table 1.

**Table 1 Tab1:** Schedule of patient evaluation

Outcome measures	Screening stage	Remedial period				Observation period
	Baseline	Day 7	Day 14	Day 21	Day 28	Day 56
Nasal symptoms	X	X	X	X	X	X
Allergy symptom score	X	X	X	X	X	X
Visual analog scale score	X	X	X	X	X	X
Rhinoconjunctivitis Quality of Life Questionnaire	X	X	X	X	X	X
Epworth Sleepiness Scale score	X	X	X	X	X	X
Tolerability of the air purifier		X	X	X	X	
Treatment compliance		X	X	X	X	
Safety assessment		X	X	X	X	X

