#### Sample size

The mean changes in findings before and after treatment were used as the indicator for efficacy evaluation in calculation of the sample size. We defined efficacy as changes in at least one score with the visual analog scale (VAS). Using a ratio of 1:1, α = 0.05, and 1 − β = 0.8 with a one-sided *t*-test, we calculated the appropriate trial sample size with 80% power. We found that a clinically significant difference could be detected using a sample of ≥21 patients in each group. We increased this number to 30 per group to allow for a predicted dropout rate of 30%.

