### Statistical analyses

Statistical analyses will be carried out using SPSS v. 17.0 (IBM, Armonk, NY, USA) in the Clinical Evaluation Center of Southern Medical University (Guangzhou, China). Data will be described as the mean and standard deviation for normally distributed data, median and interquartile range for non-normally distributed data, and frequency and proportion for categorical data. All statistical inferences will be determined using two-sided tests. We will set a significance level of 0.05 and use 95% confidence intervals to measure the uncertainty of the estimate. Efficacy analyses will use last observation carried forward (LOCF) methodology to impute for cases not fully followed up during treatment. Pearson’s χ^2^ test will be used to compare the differences between the dropout rate and the dropout rate attributable to adverse events. Baseline data analyses (two sets) will include demographic indicators and general, primary, and secondary indicators before intervention. Measurement data will be compared using a paired *t*-test. For analyses of efficacy, for quantitative variables, comparisons between groups will be made by repeated measurement variance analysis and covariance analysis. For qualitative variables, comparisons between groups will be made using Pearson’s χ^2^ test, whereas central effects will be tested by a mixed-effects model. For rating variables, comparisons between groups will be made using the Kruskal-Wallis test. In terms of analyses of centre effects, the quantitative indicators will be tested by the general linear method, and the qualitative indicators will be tested by the Cochran-Mantel-Haenszel test methods. A logistic regression model will be used to evaluate and correct the rating variables.

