The city of Yulin is part of Guangxi Province in western China, south of the Mu Us Desert. In recent years, *Artemisia desertorum* Sprengel has been sown extensively in and around Yulin, increasing the prevalence of allergic reaction [11–13]. We therefore selected Yulin as the study site. Morris et al. (2006) recommended that individuals with seasonal AR use indoor air purifiers during the ragweed-pollen season [14]. Stillerman and colleagues conducted a 12-week air-purification treatment in patients with perennial AR [15], and found that nasal congestion, sneezing, runny nose, itchy eyes, tearing, and other symptoms improved, as did quality of life. They therefore suggested that reducing allergen exposure effectively has clinical value and benefits AR patients [15]. Therapy based on reducing allergic sensitisation by avoiding allergen exposure at night may have clinical applications. Considering that plant pollen can be removed by air purification, we selected AR patients sensitive to the allergens of *Artemisia* pollen as our research subjects. The treatment periods in the studies cited above were 1–12 weeks, and the follow-up period was short, which may have resulted in inadequate evaluation of the efficacy of air-purification treatments. The duration of follow-up in our study will be 4 weeks, to ensure an adequate evaluation of treatment efficacy. In addition, those studies were not randomised controlled trials. Hence, we will conduct a double-blind, parallel-design, air purifier and placebo controlled randomised clinical trial. We expect that our study results will provide reliable evidence for determining the effects of air-purification treatment.

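### The baseline analysis names a paired t-test for two independent, unmatched arms, so the test has no defined pairs; the dropout test, as worded, also does not compare the arms

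*Protocol article*

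**What the plan says.** The Design section states that patients "will be assigned randomly to two groups of equal numbers", and the Discussion describes a "double-blind, parallel-design, air purifier and placebo controlled randomised clinical trial". No matching or crossover is mentioned.

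Three parts of the Statistical analyses section bear on the point, in this order:

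- **Dropout.** Pearson's chi-square test is to "compare the differences between the dropout rate and the dropout rate attributable to adverse events". The sentence names no treatment group.
- **Baseline.** "Baseline data analyses (two sets) will include demographic indicators and general, primary, and secondary indicators before intervention". The next sentence reads in full: "Measurement data will be compared using a paired *t*-test".
- **Efficacy.** Only then does the text turn to efficacy. For quantitative variables, "comparisons between groups will be made by repeated measurement variance analysis and covariance analysis".

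**The concern.** From its position, the paired t-test is the test for baseline measurement data. A paired test needs each value in one sample to belong with one particular value in the other. Patients in two separately randomised arms have no such link, so the stated test is not defined for comparing them. It could be run only by pairing patients arbitrarily, for instance in listing order, and the result would depend on that choice.

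The sentence may instead mean before against after within each arm. That test can be computed, but it measures change over time in one arm and says nothing about the difference between arms. The baseline comparison would then have no test for measurement data.

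The dropout sentence has a similar fault on its literal reading. Patients who leave because of adverse events are also counted among all who leave, so the two rates share patients. The chi-square test's independence assumption fails, and the result does not show whether the arms lost patients differently.

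At stake are a baseline comparison that can be reproduced and a dropout comparison that answers the usual question. Both are supporting analyses.

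**Working it through.** **The plan's own figures.** The point turns on no stated number. The group size used below is the plan's: 21 per group inflated for 30% dropout is 21 / (1 − 0.30) = 30, as the Sample size section says. The 21 cannot be reproduced because no standard deviation is given, but nothing here depends on it.

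**Paired test on independent arms**

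1. With n per arm, the paired statistic is t = (mean A − mean B) / (s_d / √n), where s_d² = s_A² + s_B² − 2·s_AB. The means and the variances s_A² and s_B² do not depend on the pairing. The covariance s_AB does, and with no natural pairs it is set by whoever lists the patients.
2. Illustration: one simulated data set, 30 per arm, SD 1, true difference 0.5 SD (assumed values). Over 5,000 random re-pairings of the same numbers, the paired p-value ran from 0.001 to 0.092 (median 0.034). The independent t-test gave a single value, 0.030.
3. With unequal arms (28 and 30 tried), the paired test could not be computed.
4. Type I error: over 20,000 simulated trials with no true difference and arbitrary pairing, the paired test rejected in 4.9% and the independent test in 4.8%.
5. Degrees of freedom: paired 30 − 1 = 29; independent 60 − 2 = 58. The two-sided 5% critical values are about 2.05 and 2.00, so this loss is minor. The fault is that the result is arbitrary.

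**Dropout test, literal reading.** The plan gives total dropout (30%) but no split by arm or cause, so the splits below are assumptions.

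1. Arms identical, 9 of 30 leaving in each (18 of 60 in all). Comparing 18/60 with the adverse-event count out of 60:

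| Adverse-event dropouts (assumed) | Chi-square | p |
|---|---|---|
| 2 | 15.36 | 0.0001 |
| 4 | 10.91 | 0.001 |
| 6 | 7.50 | 0.006 |
| 10 | 2.98 | 0.08 |

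 For 4: 120 × (18×56 − 42×4)² / (60×60×22×98) = 10.91. Three of the four results are significant although the arms do not differ.

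2. Arms clearly different, 15/30 against 3/30. Between arms: 60 × (15×27 − 15×3)² / (30×30×18×42) = 11.43, p = 0.0007. If 14 of those 18 dropouts were due to adverse events, the literal test gives 120 × (18×46 − 42×14)² / (60×60×32×88) = 0.68, p = 0.41. The difference between arms is missed.

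**Expected counts for a between-arm test, 30 per arm**

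- Total dropout at 30%: 0.30 × 30 = 9 leaving and 21 staying per arm. All are above 5, so Pearson's test is adequate.
- Adverse-event dropout: expected count per arm = total / 2, which is below 5 whenever the total is under 10. An assumed total of 2 to 8 gives 1 to 4 per arm. Only if 10 or more of the 18 predicted dropouts were due to adverse events would the count reach 5.

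**The case against.** **Efficacy is not at risk.** A reader might infer that a before/after paired test would credit the purifier with seasonal decline or placebo response. The document does not support this. The same section bases efficacy on between-group repeated-measures and covariance analyses, and no sentence makes a within-arm test the ground for an efficacy claim. This objection stands and limits the point to supporting analyses.

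**The dropout sentence may be elliptical.** It can be read as saying that each of the two rates is compared between groups, using the test that the section names for between-group comparison of qualitative variables. That reading is plausible, so it would be too strong to say that differential dropout will go untested. What stands is that the sentence does not say this, and its literal form is unsound. Nor is a test of dropout the main safeguard of validity: how the plan handles patients who leave matters more, and that is a separate question.

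**Two sets is not defined.** It may mean the two arms, but it could mean analysis sets. That the paired test compares the arms is therefore an inference from position and design. Neither meaning supplies pairs across arms.

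**Unequal arms are conditional.** Equal groups of 30 are planned, and later dropout does not erase baseline values already collected. However, the Rejection criteria and Follow-up sections remove some patients from the analysis, so the analysed arms may differ in size. Dependence on listing order remains even when they are equal.

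**No raised false-positive rate.** With equal arms and arbitrary pairing, the simulation shows none, so the point does not rest on one.

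**Conclusion.** The point holds in a limited form. As written, the plan names the wrong test for comparing baseline measurements between two independent arms: it has no defined pairs, its p-value depends on listing order, and it fails if arm sizes differ. If a within-arm test was meant, it is misplaced and leaves the baseline comparison without a test for measurement data. Confidence in this part is high, because it rests on stated text and a stated parallel design, and a separate analysis plan would not make the sentence correct.

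The dropout part holds at lower confidence, as wording that is unsound if taken literally and needs clarifying. The splits used to illustrate it are assumptions.

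The effect is confined to the baseline and dropout comparisons. The primary efficacy comparison, its stated between-group methods and the sample size do not change. The correction should be made, but the trial's main result does not depend on it.

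**What to change.** 1. **Baseline.** Replace the paired-test sentence with a description of baseline data by arm (mean and SD, or median and interquartile range). If a test is kept, use the independent two-sample t-test, or the Wilcoxon rank-sum test for non-normal data. Say what the two sets are.
2. **Before/after, if that was meant.** Move the paired test out of the baseline passage, label it descriptive, and state that efficacy rests on the between-group analyses already named.
3. **Dropout.** Reword so that total dropout and adverse-event dropout are each compared between the two arms. Keep Pearson's chi-square where expected counts are at least 5 and use Fisher's exact test where they are lower, which is likely only for adverse-event dropout. A 95% interval for each difference fits the section's stated use of confidence intervals.

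The cost is a few sentences in the analysis plan. No new data, visits or patients are needed, and no power figure changes.

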**Methods:**

This is a randomized, double-blind, clinical controlled trial that will test active and inactive versions of an air purifier (Atmosphere®; Amway China). Sixty AR patients sensitive to the allergens produced by *Artemisia* pollen will be assigned randomly to two groups of equal numbers. All patients will undergo a 4-week treatment period and a 4-week observation period. Evaluation will be conducted at baseline (day 0) and on days 7, 14, 21, 28, and 56. The primary outcome measure will be the difference in visual analog scale scores from baseline. Secondary outcomes will be changes from baseline in nasal symptoms, allergy symptom scores, responses to the Rhinoconjunctivitis Quality of Life Questionnaire, Epworth Sleepiness Scale scores, and tolerability scores for the air purifier. Side effects of treatment will be recorded.

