#### Allergy symptom scores

Allergy symptom scores will be used to grade symptoms as 0 (“no symptoms”), 1 (“mild symptoms”), 2 (“moderate symptoms”), and 3 (“severe symptoms”). The symptoms graded will be congestion, sneezing, nasal itch, rhinorrhea, eye itch, ear/palate itch, eye redness, and tearing.

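### The test fixed for ordinal secondary outcomes takes no baseline covariate and gives no interval, and the logistic-model sentence is too loose to be relied on for either

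*Protocol article*

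**What the plan says.** All of the analysis text is in the Statistical analyses section of the protocol article.

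- Ordinal outcomes: "For rating variables, comparisons between groups will be made using the Kruskal-Wallis test".
- Two sentences later, directly after the methods for centre effects: "A logistic regression model will be used to evaluate and correct the rating variables".
- Quantitative outcomes, by contrast: "comparisons between groups will be made by repeated measurement variance analysis and covariance analysis".
- For all outcomes: "All statistical inferences will be determined using two-sided tests", and "We will set a significance level of 0.05 and use 95% confidence intervals to measure the uncertainty of the estimate".

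The abstract defines the outcomes as changes: "Secondary outcomes will be changes from baseline in nasal symptoms, allergy symptom scores". Nasal symptoms are represented by turbinate swelling on three grades, 1 to 3. Allergy symptoms are graded 0 to 3 on eight items: "The symptoms graded will be congestion, sneezing, nasal itch, rhinorrhea, eye itch, ear/palate itch, eye redness, and tearing". Table 1 schedules both at baseline and at days 7, 14, 21, 28 and 56, and the data collection section lists both among the baseline variables. The article does not say which named outcomes count as rating variables.

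**The concern.** Baseline grades are collected and the outcomes are defined relative to baseline, but the named test has no place for a covariate. There are two ways to run it. On the follow-up grade, it leaves baseline out. On the change in grade, baseline enters by subtraction only: a move from 3 to 2 counts the same as a move from 2 to 1, and a patient who starts at turbinate grade 1 cannot improve. Neither version gives an effect measure to which an interval could be attached.

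The logistic sentence can be read in two ways. If it belongs to the centre-effects text before it, no baseline-adjusted efficacy analysis of the ordinal outcomes is stated. If it is an efficacy model, those outcomes have two analyses and the article does not say which is the main one. At stake are power and a reportable effect size for the ordinal secondary outcomes.

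**Working it through.** **The plan's own figures.** The article gives no power figure for the ordinal outcomes, so there is none to reproduce. Its sample size concerns the VAS: at least 21 per group, raised for 30% dropout to 21 / (1 − 0.30) = 30. Those two numbers serve below as the group sizes without and with full dropout.

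**From the article.** Group sizes 30 and 21; three grades (turbinate) or four (single symptoms); two-sided 5% level.

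**Assumed, because the article gives no value.** Treatment shift on the latent scale, correlation ρ between baseline and follow-up latent scores, and grade cut points.

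**Model.** Baseline score b ~ N(0,1). Follow-up score y = ρ·b + √(1 − ρ²)·e − δ·arm, with e ~ N(0,1). Both scores are cut into three about equally likely grades at −0.43 and 0.43, with δ = 0.8 SD and one follow-up visit. There were 800 simulated trials per row, so the Monte Carlo error of each power is about 1.5 to 2 points.

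**Tests.** (a) Kruskal-Wallis on the follow-up grade. (b) Kruskal-Wallis on the change in grade. (c) Proportional odds, logit P(Y ≤ k) = θₖ − (β·arm + γ·baseline grade), with a likelihood-ratio test of β (reject if 2 × log-likelihood difference > 3.841).

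| n per group | ρ | (a) KW grade | (b) KW change | (c) adjusted PO | c − a | c − b |
|---|---|---|---|---|---|---|
| 30 | 0 | 74.3% | 43.0% | 75.9% | 2 | 33 |
| 30 | 0.3 | 76.5% | 54.9% | 79.5% | 3 | 25 |
| 30 | 0.5 | 76.9% | 62.3% | 84.6% | 8 | 22 |
| 30 | 0.7 | 73.4% | 75.5% | 88.6% | 15 | 13 |
| 21 | 0 | 59.6% | 30.4% | 61.3% | 2 | 31 |
| 21 | 0.3 | 58.4% | 40.3% | 63.0% | 5 | 23 |
| 21 | 0.5 | 61.6% | 47.8% | 70.8% | 9 | 23 |
| 21 | 0.7 | 64.1% | 62.1% | 81.1% | 17 | 19 |

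**Sensitivity to the shift and the number of grades** (30 per group, δ = 0.7 SD; a / b / c):

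- Three grades, 500 trials: 65 / 37 / 66% at ρ = 0; 65 / 54 / 74% at 0.5; 66 / 68 / 82% at 0.7.
- Three grades, 2,000 trials: 66 / 53 / 74% at 0.5; 67 / 66 / 83% at 0.7.
- Three grades, 600 trials, a and c only: 68 / 68% at 0; 65 / 67% at 0.3; 66 / 72% at 0.5.
- Four grades, 2,000 trials: 71 / 63 / 80% at 0.5; 72 / 79 / 90% at 0.7.

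The adjusted model was not behind either Kruskal-Wallis version in any scenario. Its lead over (a) ranges from 68 − 68 = 0 points to 90 − 72 = 18. Its lead over (b) ranges from 90 − 79 = 11 points to 33.

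**False positives with no treatment effect.** With 30 per group, ρ = 0 and 0.7 and 500 trials, all three tests rejected in 3.8 to 5.8% of trials. In the 2,000-trial runs, Kruskal-Wallis rejected in 4.4 to 5.8% and proportional odds in 5.4 to 6.2%. A small part of the power gap may therefore come from a slightly liberal likelihood-ratio test.

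**The case against.** The strongest reply is that the plan may already contain the remedy. Kruskal-Wallis on the change does use baseline. A logistic model that corrects these variables may mean covariate adjustment, and it would normally give an odds ratio with an interval. A proportional-odds model is itself a logistic model. The article condenses a fuller protocol, and model type, covariates and visit are commonly left to the full protocol or the SAP. A rank test followed by an adjusted model is no contradiction.

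Much of this stands. A reader might infer that baseline is never used, or that no interval will ever be produced. The article supports neither, because of the change definition and the logistic sentence. A reader might also infer that the grades will be dichotomised, but no cut point appears anywhere. Nor can the point be extended to every secondary outcome: RQLQ, Epworth and a summed symptom score may count as quantitative, where covariance analysis is planned, and Table 1 schedules no baseline tolerability assessment. With low correlation, the loss against Kruskal-Wallis on the final grade is negligible.

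What does not fall away is that the article itself fixes the between-group comparison for ordinal outcomes, and fixes it as a test with no covariate and no effect estimate. That is a stated choice rather than a detail left open. The logistic sentence cannot be relied on to repair it while it may concern centre effects only.

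**Conclusion.** The point holds as an efficiency and reporting weakness, limited to outcomes analysed as ordinal: the turbinate grade, and the single symptom grades if they are not summed. Compared with a baseline-adjusted proportional-odds model, Kruskal-Wallis on the final grade gives up about 0 to 2 points of power at correlation 0, about 8 at 0.5 and about 15 at 0.7. Kruskal-Wallis on the change, which is closest to the abstract's definition, gives up about 15 to 30 points in most scenarios. The direction was stable across the scenarios. The sizes rest on assumed shifts of 0.7 to 0.8 SD, assumed cut points and a latent correlation that the article does not give; they also come from a single follow-up visit.

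A reader might go further and call the stated test invalid. That is not supported: with two groups it is a sound rank test, its simulated false-positive rate was near 5%, and the outcomes are secondary.

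**What to change.** Replace the Kruskal-Wallis and logistic sentences with one rule. It should name the outcomes treated as ordinal. For each, the main between-group analysis is a proportional-odds logistic model of the day-28 grade with arm and baseline grade, reporting the common odds ratio with its 95% CI. Kruskal-Wallis stays as a supportive check. If the logistic sentence was meant for centre effects, say so separately.

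If all treatment visits (days 7, 14, 21 and 28) are modelled together, include an arm-by-visit term; without it the model estimates an average over visits and gives no day-28 effect. Fix one approach, for example GEE, because a random-effects model and GEE estimate different odds ratios (conditional and marginal).

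The cost is wording and some analysis work. No new data are needed, since baseline grades are already scheduled. The downsides are that the proportional-odds assumption has to be checked and that, with at most 60 patients, sparsely filled grades may need attention, more so in a repeated-measures version.

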### Setting

Study activities will be conducted at different settings. Patient enrollment and specimen and data collection will be conducted in the Outpatient Department of the First Hospital of Yulin (Guangxi, China). Biochemical examinations will be undertaken by King Med Diagnostics (Guangzhou, China). Data analyses will be performed at the University of Toronto (Toronto, ON, Canada).

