### Trial status

This clinical trial was reviewed by the Ethics Committee of the First Hospital of Yulin in 2016. The first patient was enrolled in 2016. From the middle of 2016 to the end of 2017, 45 patients completed the treatment and observation periods. This clinical trial is expected to be completed at the end of 2018.

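### Centre-effect analyses are planned for a trial with one recruiting site, where no centre effect can be estimated; enrolment period is the more useful factor to pre-specify

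*Protocol article*

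**What the plan says.** The protocol article, Statistical analyses, plans centre-effect work in two places. In the sentence on qualitative variables it says "whereas central effects will be tested by a mixed-effects model". Two sentences later it says "In terms of analyses of centre effects, the quantitative indicators will be tested by the general linear method" and, for the other type of outcome, "the qualitative indicators will be tested by the Cochran-Mantel-Haenszel test methods".

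The Setting section says "Patient enrollment and specimen and data collection will be conducted in the Outpatient Department of the First Hospital of Yulin". The other places listed there are a laboratory and a data-analysis location, and neither recruits patients. The Discussion confirms the single location: "We therefore selected Yulin as the study site".

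On the calendar, Trial status reports "From the middle of 2016 to the end of 2017, 45 patients completed the treatment and observation periods" and adds "This clinical trial is expected to be completed at the end of 2018". For quantitative efficacy variables, Statistical analyses says "comparisons between groups will be made by repeated measurement variance analysis and covariance analysis"; it names no covariate.

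**The concern.** A centre effect is a difference between centres. If every patient is enrolled and assessed in one outpatient department, there is no such difference to estimate, and part of the written plan cannot be carried out. This is text stated in the article, not a detail left for a later document to supply, so an unseen SAP could not make it right while the trial has one site.

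The plan thus provides for a grouping factor that does not vary and names none for calendar time, which does. Patients are selected for *Artemisia* pollen sensitivity, those sensitive to indoor allergens are excluded, and each is treated for only 4 weeks. How much pollen a patient meets in those weeks may depend on when they fall. What is at stake is some precision in the primary VAS comparison, and protection against the two arms differing by chance in when their patients were treated.

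**Working it through.** **1. Centre count against planned analyses**

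| Item | Source | Value |
|---|---|---|
| Recruiting centres | Setting; Discussion | 1 |
| Centre analyses, explicit | Statistical analyses | 2 (general linear method; Cochran-Mantel-Haenszel) |
| Centre analyses, if central means centre | Statistical analyses | 3 (adding the mixed-effects model) |

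- General linear method: degrees of freedom for centre = number of centres − 1 = 1 − 1 = 0. No effect is estimable.
- Mixed-effects model with centre as a random effect: one level gives no information on between-centre variance.
- Cochran-Mantel-Haenszel by centre: one stratum. For a two-by-two table the statistic without continuity correction is (N − 1)/N times Pearson's chi-square. With N = 60 the factor is 59/60 = 0.983. The test runs, but it repeats the Pearson test already planned for qualitative variables.

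**2. The plan's own sample-size figure**

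The Sample size section gives 21 per group, raised to 30 for 30% dropout: 21/(1 − 0.30) = 30. This reproduces. The 21 itself cannot be checked, because no standard deviation is given. It can only be inverted. With n = 21 per group, a one-sided 5% *t*-test and 80% power, the noncentral *t* gives a standardised difference d = 0.781. If the target is read as 1 VAS point, the SD is 1/0.781 = 1.28.

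**3. What adjusting for enrolment period could be worth (illustration)**

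Inputs: d = 0.781 (back-solved, not stated); n = 21 per group (Sample size); two-sided 5% test (Statistical analyses); R² = share of the variance in VAS change explained by period (assumed, since the article gives nothing to fix it).

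Formulae: d_eff = d/√(1 − R²); noncentrality = d_eff × √(n/2) = d_eff × √10.5; degrees of freedom 2 × 21 − 2 = 40; critical value 2.021.

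| Assumed R² | d_eff | Noncentrality | Two-sided power |
|---|---|---|---|
| 0% | 0.781 | 2.531 | 69% |
| 5% | 0.801 | 2.596 | 72% |
| 10% | 0.823 | 2.668 | 74% |
| 20% | 0.873 | 2.829 | 79% |
| 30% | 0.933 | 3.025 | 84% |

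Taking 2 degrees of freedom for period (40 down to 38) lowers each power by about 0.001.

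The 69% starting point is below 80% only because the sample size used a one-sided test and the analysis is two-sided. That is a separate matter; only the change down the table belongs to this point.

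**4. Chance imbalance (illustration)**

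Assume three equal enrolment periods of 20 patients and 30 patients per arm, with no stratification by period. The number from one given period falling in one arm is hypergeometric. A gap of at least 20 percentage points between arms in that period's share means a split of 13 to 7 or more extreme, since (13 − 7)/30 = 0.20. The probability is about 17%.

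**The case against.** The strongest reply concerns the season half. A reader might infer that pollen season is the true clustering factor and that the plan wrongly left it out of its model. The article does not support that:

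- It names covariance analysis with no covariates at all, not even baseline VAS. A covariate list is commonly left to the SAP, which is not shown, so no stated model exists from which season was dropped.
- It gives no local pollen calendar, no enrolment dates within a year and no between-season variance in VAS. That some patients were treated out of season is conjecture.
- Randomisation is by individual. Omitting a prognostic factor such as season does not bias the arm comparison.
- The end of 2018 is the expected completion of the trial. With 8 weeks per patient, recruitment must end earlier, and no recruitment end date is given.
- The power gain depends on an assumed R². Season may shift baseline and later VAS alike, so analysing change or adjusting for baseline could already remove part of it.

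All of this stands, and it limits the season element to a recommendation.

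On the centre half, the reply is that Cochran-Mantel-Haenszel with one stratum can be computed, that it is a standard test when centre is merely to be accounted for, that central effects may not mean centre effects, and that the VAS comparison does not depend on these sentences. Each point is fair. None removes the contradiction: on any reading at least two centre analyses are planned and one site is described.

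**Conclusion.** The contradiction between Setting and Discussion on one side and Statistical analyses on the other is real and rests on no assumption beyond the site description being complete. The centre term has 0 degrees of freedom, and the stratified test collapses to one stratum. The planned comparison of arms on VAS can still be run, so the direct harm is confined to text that cannot be executed or is redundant.

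Using enrolment period in place of centre is a worthwhile improvement, not the correction of a second error. The basis is a pollen-driven condition treated across at least 2016 and 2017, with 45 completers in that span and completion expected at the end of 2018. The possible gain runs from nothing (R² = 0%) to about 15 percentage points of power (69% to 84% at R² = 30%). It rests on the back-solved d = 0.781, 21 evaluable patients per group and the assumed R².

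**What to change.** 1. Delete the centre-effect sentences from Statistical analyses, including the one on central effects if it means centre. If other centres do recruit, name them in Setting instead.
2. Pre-specify enrolment year or pollen-season period, derived from the enrolment date, as a fixed factor in the primary VAS covariance analysis. Define the periods before unblinding and without reference to outcomes.
3. Use the same factor as the stratum when the Cochran-Mantel-Haenszel test compares treatment groups on qualitative outcomes.
4. An analysis limited to patients whose 28 treatment days fell inside the local *Artemisia* season is optional and exploratory. It needs season dates that the article does not give and would shrink a 60-patient trial.

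The cost is a change of wording and 1 to 2 degrees of freedom for two or three periods. No new patients or assessments are needed, assuming that enrolment dates are on record; the article's list of baseline variables does not mention them.
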